### Study setting and procedure

All participants will be college students with insomnia admitted to the main campus (Shipai campus) of Jinan University, Guangzhou City, China. One hundred participants meeting the trial criteria will be included and randomly assigned to the standard TCPS group or three sham-controlled *Post Standing* groups according to a 1:1:1:1 allocation ratio with allocation concealment. The training regimen will include both centralized (two weeks) and supervised (12 weeks) training and a follow-up period of eight weeks, i.e., a total study duration of 22 weeks.

The primary outcomes will be measured using EEG data [24–27] and Pittsburgh Sleep Quality Index (PSQI) scores [28, 29] to evaluate central nervous system (CNS) bioelectrical activity and sleep quality, respectively. The secondary outcomes will include Insomnia Severity Index (ISI) scores [30, 31], 36-Item Short Form Health Survey Questionnaire (SF-36) scores [32, 33], plantar pressure and biomechanical equilibrium [34, 35], and physical function including respiratory function [36, 37], HRV [38, 39], blood pressure [40, 41], and blood oxygen saturation [42, 43].

All outcomes will be measured at baseline, at eight weeks (at the mid-point of supervised training), and at 14 weeks (at the end of supervised training). Sleep quality and quality of life will also be evaluated during the four- and eight-week follow-up periods. All measurements will be conducted in a professional exercise and human science laboratory. The study design is shown in Fig. 1 and the timetable is shown in Table 1.

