### Sample size estimation

Sample size calculations were performed a priori using G-Power Software (v3.1.9.7, Germany). Due to limited previous studies on the use of *Post Standing* or other Qigong exercises in participants with insomnia, the effect size calculation was based on the best available data regarding the hypothesized change in PSQI score found in the literature. The PSQI effect size ranged from 0.31 to 0.83, so we adopted a conservative estimate of 0.31 for our calculation [44]. An F-test ANOVA (repeated measures, within-between interaction) was used for four groups and three measurements. The desired power was set at 80%, with a two-sided α error probability of 0.05. This resulted in a required sample size of 80 participants. Considering a potential attrition rate of 20%, we aim to recruit a minimum of 100 participants for this study. To allocate an equal number of participants to each arm (1:1:1:1), a minimum of 25 participants per arm is necessary.

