#### Statistical analysis

We will use IBM SPSS Statistics 25.0 (IBM Statistics, Armonk, NY) for statistical analysis, with a significance threshold of 0.05 and 95% confidence intervals for all estimates. Categorical variables will be reported as frequencies or percentages, while continuous variables will be described using mean ± standard deviation for normally distributed data and median [interquartile range (IQR)] for non-normally distributed data. We will conduct intention-to-treat (ITT) and per-protocol (PP) analyses for all outcomes. If ITT and PP results are consistent, we will consider them reliable; otherwise, ITT results will be preferred. For missing data, we will use multiple imputation and last observation carried forward analysis. Baseline demographic characteristics will be compared between groups using analysis of variance (ANOVA), non-parametric Wilcoxon signed rank, or chi-squared tests. Adjusted analysis with multiple linear regression or logistic regression will be performed if potential confounding factors are present. Repeated-measures ANOVA (group × time) will be conducted to compare outcome measures between the standardized TCPS and sham-controlled *Post Standing* groups and within the standardized TCPS group at different assessment time points. Safety will be assessed by recording and reporting adverse events for each group. A chi-squared or Fisher's exact test will be used to compare frequency differences in adverse events between groups, and severe adverse events will be described in detail. Logistic regression and linear mixed-effects models will be employed to explore factors affecting adherence and feasibility, adjusted for confounders. Adherence-related data will be obtained from training self-evaluation logs and sign-in sheets.

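### Covariate adjustment hangs on undefined confounding factors, a paired test is named for four independent arms, and baseline PSQI appears as an outcome level instead of a covariate

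*Protocol article*

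**What the plan says.** Three statements in the Statistical analysis section bear on this.

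- Baseline comparison: "Baseline demographic characteristics will be compared between groups using analysis of variance (ANOVA), non-parametric Wilcoxon signed rank, or chi-squared tests".
- Adjustment, in the next sentence: "Adjusted analysis with multiple linear regression or logistic regression will be performed if potential confounding factors are present". No criterion, threshold or covariate list follows.
- Main comparison: "Repeated-measures ANOVA (group × time) will be conducted to compare outcome measures". It carries no condition and names no baseline covariate.

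Two other sections show how baseline enters the main comparison. Study setting and procedure states: "All outcomes will be measured at baseline, at eight weeks (at the mid-point of supervised training), and at 14 weeks". Sample size estimation states: "An F-test ANOVA (repeated measures, within-between interaction) was used for four groups and three measurements". Baseline, week 8 and week 14 make three, so baseline appears to be one of the repeated measurements. The article does not say so outright.

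**The concern.** There are three separate weaknesses.

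1. **A test that does not fit the design.** Signed rank needs paired observations or a single sample. The trial has four parallel, independent arms, for which the rank-based counterpart of one-way ANOVA is Kruskal-Wallis. More generally, baseline differences between randomised arms arise by chance, so testing them answers no useful question.

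2. **An open adjustment rule.** Whether confounding factors are present can only be judged from the data. The rule as written settles neither whether an adjusted result will exist nor which covariates produce it. It also does not confine the covariates to variables measured before randomisation.

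3. **Precision left unused.** If baseline PSQI is a level of the time factor, the group × time interaction compares changes from baseline between arms. Using baseline as a covariate estimates the same treatment effect with variance that is no larger. After the allowed attrition the plan has 80/4 = 20 participants per arm, so precision is scarce.

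**Working it through.** **The plan's own figure.** "The PSQI effect size ranged from 0.31 to 0.83, so we adopted a conservative estimate of 0.31 for our calculation"; "The desired power was set at 80%, with a two-sided α error probability of 0.05"; "This resulted in a required sample size of 80 participants". Read 0.31 as Cohen's f (the article does not state the metric), with k = 4 groups and m = 3 measurements. The interaction test has

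- df1 = (k−1)(m−1) = 6
- df2 = (N−k)(m−1)
- noncentrality λ = f²(N−k)(m−1), which is G*Power's effect-size option *as in SPSS*.

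Power first reaches 0.80 at N = 78. The next multiple of four is 80, where λ = 0.0961 × 76 × 2 = 14.6 and power is 0.813. Then 80/(1 − 0.20) = 100. The stated size therefore reproduces under this option. G*Power's default option with a correlation of 0.5 would give 28, and the article does not say which was used. What matters here is that the calculation is for an interaction over three measurements, which supports reading baseline as a repeated level.

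**Variance of the treatment contrast at one post-baseline time.** Let the outcome variance be 1 at both times and ρ the correlation between baseline and follow-up.

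- Change from baseline: 2(1−ρ)
- Follow-up adjusted for baseline: 1−ρ²
- Ratio: (1−ρ²)/[2(1−ρ)] = (1+ρ)/2

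Equal variances are not needed for the direction. With standard deviations s₀ at baseline and s₁ at follow-up, the change variance is s₀² + s₁² − 2ρs₀s₁ and the adjusted variance is s₁²(1−ρ²). The difference is (s₀ − ρs₁)², which is never negative.

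**Assumptions for the numbers.** The article gives no ρ, so 0.3, 0.5 and 0.7 are assumed. The standardised difference d = 0.5 is also assumed. The comparison is 20 against 20, two-sided 0.05, by noncentral t, with 38 degrees of freedom for change and 37 for the adjusted analysis. The noncentrality is d/√(v × 2/20), where v is the variance above.

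| ρ | v, change | v, adjusted | Ratio | Saving | Power, change | Power, adjusted |
|---|---|---|---|---|---|---|
| 0.3 | 1.40 | 0.91 | 0.65 | 35% | 0.256 | 0.365 |
| 0.5 | 1.00 | 0.75 | 0.75 | 25% | 0.338 | 0.428 |
| 0.7 | 0.60 | 0.51 | 0.85 | 15% | 0.512 | 0.578 |

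For example, at ρ = 0.5 the noncentrality rises from 0.5/√0.100 = 1.58 to 0.5/√0.075 = 1.83. In terms of numbers, 80 × 0.75 = 60 analysed participants with adjustment would match 80 with change scores. At ρ = 0.3 the matching number is 52, and at 0.7 it is 68.

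**The case against.** The case on the other side is that this is a modest wording matter, and several parts of it stand.

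- **Trigger.** A reader might infer that a significant baseline test switches adjustment on. The article does not say this. The two sentences are only adjacent, and the tests cover demographic characteristics, not PSQI.
- **Primary model.** A reader might also infer that the primary model itself depends on the data. The group × time ANOVA is stated without condition, and nothing says the adjusted regression replaces it. The natural reading is a fixed main analysis with a loosely defined adjusted one beside it.
- **Baseline is used.** As a repeated level it does contribute, and the change-type comparison is valid under randomisation. The loss is relative to covariate adjustment, not relative to ignoring baseline.
- **Diary activity.** Participants record physical activity during training to deal with bias from excessive activity (Training quality monitoring and duration). One might infer that this post-randomisation variable will enter the efficacy model. The Statistical analysis section names no such covariate, so this is only something the wording fails to exclude.
- **Reach of the wrong test.** Signed rank appears only for baseline characteristics and affects no efficacy estimate.
- **Separate analysis plan.** Detailed covariate lists are commonly left to one. That excuses the missing list. It does not excuse a stated rule that makes adjustment conditional, nor a named test that cannot be applied.

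**Conclusion.** The point holds in a limited form. The signed-rank test is an error in the text. The adjustment rule is conditional on something undefined. Baseline PSQI appears, from three sections read together, to enter as an outcome level, where covariate adjustment would be at least as precise apart from one degree of freedom.

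The illustrative saving in variance is 15% to 35% for assumed correlations of 0.7 down to 0.3. A flat figure of one quarter would need a correlation of 0.5, which the article does not give. The power figures describe a two-arm contrast at a single time with an assumed d of 0.5. They are not the power of the planned four-group, three-measurement test. The validity of the randomised comparison is not in question. The change is worth making because it gains precision and closes an open choice at practically no cost.

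**What to change.** In the Statistical analysis section:

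1. Report baseline characteristics by arm descriptively and delete the significance tests. If a rank-based test is kept, name Kruskal-Wallis in place of Wilcoxon signed rank.
2. Model the post-baseline PSQI values with baseline PSQI as a covariate, whatever imbalance is observed, and treat each other outcome the same way with its own baseline. State that the treatment effect is then the between-arm contrast at the post-baseline times, because baseline is no longer a level of the time factor.
3. Replace the conditional adjustment sentence with this prespecified rule, and limit any further covariates to named variables measured before randomisation.

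The schedule already collects baseline PSQI and the other baseline outcomes. Recruitment, visits and measurements stay as they are, and only the analysis wording changes.

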Our primary hypothesis is that TCPS will improve sleep quality and quality of life of college students with insomnia compared with students engaging in sham-controlled *Post Standing* practice and that it will be safe, acceptable, and feasible. Our secondary hypotheses are that (i) the mind adjustment of TCPS will increase alpha and theta frequencies in specific brain regions, particularly in the alpha band, and enhance functional connectivity prior to observable improvements in sleep quality; and (ii) engaging in TCPS will modulate HRV, respiratory function, blood pressure, and oxygen saturation due to body and breath adjustments. Ultimately, we also expect TCPS to improve sleep quality and overall quality of life of students with insomnia following the intervention.

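### The primary hypothesis is TCPS better than sham, but the only named and powered efficacy test is a four-arm group-by-time interaction, joined to a comparison within the TCPS arm that has no comparator

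*Protocol article*

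**What the plan says.** All references are to the protocol article.

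- **Hypothesis (Introduction).** The primary hypothesis is comparative and has a direction: "TCPS will improve sleep quality and quality of life of college students with insomnia compared with students engaging in sham-controlled" practice.
- **Analysis (Statistical analysis).** One efficacy test is named: "Repeated-measures ANOVA (group × time) will be conducted to compare outcome measures between the standardized TCPS and sham-controlled" groups. The sentence continues: "and within the standardized TCPS group at different assessment time points". The significance threshold is 0.05 throughout.
- **Sample size (Sample size estimation).** "An F-test ANOVA (repeated measures, within-between interaction) was used for four groups and three measurements". The effect size comes from the literature: "The PSQI effect size ranged from 0.31 to 0.83, so we adopted a conservative estimate of 0.31 for our calculation". Also: "The desired power was set at 80%, with a two-sided α error probability of 0.05". The result is 80 evaluable participants, raised to 100 for 20% attrition, or 25 per arm.
- **Design (Table 1 and Discussion).** The arms cross posture (TCPS or normal standing) with breathing (abdominal or natural chest). The Discussion says the three shams are there to show the benefit of combining the two.
- **Features that raise improvement in every arm.** Entry requires PSQI above 5 and ISI above 7 (Eligibility criteria). All arms have 14 weeks of coached sessions (Training quality monitoring and duration). Coaches tell every participant that any of the forms may help (Blinding method).

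**The concern.** The interaction of four groups with three visits has (4−1)(3−1) = 6 numerator degrees of freedom and no direction. It responds to any arm departing from the others at any visit, including a sham doing best or only the weakest sham lagging. By itself it does not answer whether TCPS is better than sham, yet it is the only test the article names and the one that sets the sample size.

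The within-TCPS comparison has the opposite weakness. It looks at the right arm but has no comparator, so it mixes any specific effect with regression to the mean after selection on the outcome scale, with expectation, and with the general effect of coached practice. The three sham arms exist to remove exactly these components.

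At stake is the headline conclusion. If the paper reports a significant interaction and a significant fall in PSQI within TCPS, neither result establishes superiority over sham.

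**Working it through.** **1. The article's own figure.** Inputs from Sample size estimation: k = 4 groups, m = 3 measurements, effect 0.31, alpha 0.05, power 80%. Reading 0.31 as Cohen's f, with λ = f²(N−k)(m−1), df1 = 6 and df2 = (N−4)(2):

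- N = 76: λ = 0.0961 × 72 × 2 = 13.84, power 0.787.
- N = 80: λ = 0.0961 × 76 × 2 = 14.61, df2 = 152, critical F = 2.159, power 0.813.

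So 80 is reproduced, and 80/(1−0.20) = 100. The match is not unique, because the article gives neither the software option nor the correlation; other settings also return 80. The arithmetic is not in dispute. The issue is what the test targets.

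**2. What a significant interaction means.** Assumptions: n = 20 per arm, unit SD, compound symmetry with correlation ρ, and only sham II improving, by 0.83 SD (the upper literature value, used as an SD shift). With one arm of four changing, the interaction sum of squares is 0.75 × Σ(x_t − x̄)² over that arm's visits, and λ = n × SS/(1−ρ).

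- Linear course (0, 0.415, 0.83): SS = 0.75 × 0.3445 = 0.2583; at ρ = 0.5, λ = 20 × 0.2583/0.5 = 10.33; power 0.64 (0.63 by simulation).
- Step change (0, 0.83, 0.83): SS = 0.75 × 0.4593 = 0.3445; λ = 13.78; power 0.79 (0.79 by simulation).

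The figure depends on ρ. For a linear 0.8 SD change in sham II alone, simulation with 10,000 replicates gives 44%, 60% and 85% at ρ = 0.3, 0.5 and 0.7. The interaction is significant with TCPS beating no sham in 41%, 56% and 81%.

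**3. What a significant within-TCPS change means.** Suppose every arm improves equally by 0.67 SD of change, for example a 2-point PSQI fall with an SD of change of 3 (both assumed). A pre-post paired t-test in TCPS at n = 20 has noncentrality 0.667 × √20 = 2.98 against a critical value of 2.093, which gives power 0.81. With 25 it is 0.89. The article does not name a paired t-test, so the time F-test within TCPS was also simulated, with an equal linear improvement of 0.5 SD in all arms: 35%, 48% and 70% at ρ = 0.3, 0.5 and 0.7. The group-by-time test stays at about 5%, as it should.

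**4. Power for the question actually asked.** Normal approximation, 20 evaluable per arm. For a pairwise contrast, power = Φ(d√(20/2) − z). For TCPS against the three shams pooled, the first term is d/√(1/20 + 1/60) = 3.873d.

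| d | pairwise, 0.05 | pairwise, 0.05/3 | pooled 1:3, 0.05 |
|---|---|---|---|
| 0.31 | 16% | 8% | 22% |
| 0.62 | 50% | 33% | 67% |
| 0.83 | 75% | 59% | 90% |

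Example: 0.31 × 3.162 − 1.960 = −0.980, so power is 16%. The evaluable number per arm for 80% pairwise power at 0.05 (at 0.05/3) is 164 (218), 41 (55) and 23 (31). The row d = 0.62 reads 0.31 as f with two groups (d = 2f). Which metric the article means is an assumption, and d applies to the score analysed.

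**The case against.** The strongest reply is that the article does aim the ANOVA at TCPS versus sham, since the sentence says so, and that the contrast, primary visit and adjustment may stand in an analysis plan that is not shown. That is fair. It rules out the reading that the trial cannot show superiority; only the omnibus test taken alone cannot. It does not remove the point, because the article itself fixes the interaction as the basis of the sample size and lists the within-TCPS comparison among the outcome analyses.

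Several stronger readings are tempting and are not supported:

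- **That pairwise follow-up will be unadjusted, or that within-TCPS change will be claimed as efficacy.** The article says neither. Its efficacy statements are mostly framed against sham. One closing sentence of the hypotheses expects improvement without naming a comparator, but it follows the sham-controlled primary hypothesis.
- **That 63% to 79% is a false-positive rate for TCPS.** It is not. A significant interaction followed by an unadjusted pairwise win for TCPS, when TCPS adds nothing, occurs in only about 1% to 4% of simulated trials.
- **That three uncorrected comparisons inflate the error in TCPS's favour to 12.6%.** That figure is two-sided and counts wins for sham. In TCPS's favour it is about 6%.
- **That a significant interaction when TCPS and sham II improve equally is an error (88% in a simulation at 0.8 SD).** In that scenario TCPS truly beats shams I and III; only its equality with sham II is hidden.

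**Conclusion.** The concern holds in a limited form. The named and powered test does not match the directional primary hypothesis: on its own it shows that some arm's course differs, and it can readily be significant when only a sham improves. The added within-TCPS comparison is not evidence of a specific effect. The percentages rest on assumed SDs, correlations, effect sizes and time courses that the article does not give; the mismatch between test and hypothesis does not depend on them. The documents do not show that the authors intend a false claim, nor that the error rate of a sensible follow-up would be high. What they do show is that the comparison carrying the conclusion is not identified and that the 80% power belongs to a different test.

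**What to change.** State one primary analysis of PSQI: a 1-df TCPS-versus-sham contrast at week 14, from a repeated-measures model adjusted for baseline. Choose and write down one of these forms:

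- **TCPS against each sham.** If a win over any one sham counts, control multiplicity over three comparisons (Dunnett is one option). If all three wins are required, no adjustment is needed.
- **One contrast.** Either TCPS against the pooled shams, or a factorial contrast that follows the posture-by-breathing layout. The synergy contrast (TCPS − I − II + III) answers a different question and has variance 4σ²/n, against 2σ²/n for a pairwise contrast.

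Treat weeks 8, 18 and 22 as secondary, the omnibus interaction as supportive, and within-TCPS change as descriptive with a confidence interval.

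**Cost.** The wording change is small and can be made before data are unblinded, but the power statement must be redone for the chosen contrast. At 20 evaluable per arm it ranges, on the assumptions above, from 8% to 75% for a pairwise contrast and from 22% to 90% for the pooled one. Requiring all three wins gives about 47% when only TCPS improves, by 0.8 SD with a linear course and ρ = 0.5 (simulation). Baseline adjustment may recover some power. If the restated figure is too low, the sponsor must either enlarge the trial or say plainly what it can and cannot detect.

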## Discussion

This protocol describes the first double-blind parallel RCT aiming to evaluate the efficacy, safety, and feasibility of using TCPS for sleep quality improvement in college students with insomnia. Compared with the diverse Qigong modalities used to treat insomnia in the literature, using TCPS to treat insomnia in college students has the following advantages. First, TCPS is a static form of Qigong that requires minimal space and can be practiced by college students in places like dormitories or outdoors. It can also be easily incorporated into the study day, such as during the commute or study breaks, thereby encouraging its practical application. Second, TCPS is easy to learn and has a low risk of injury, contingent upon adherence to the correct taught posture and respiratory principles. This makes it optimal for independent and persistent practice by college students. Third, within the university milieu, insomnia tends to emerge as a consequence of the psychophysiological consequences of academic obligations and sociocultural interactions. Our previous research has shown that TCPS has therapeutic effects on anxiety symptoms in the college population through regulation of respiratory function, correction of body balance, and augmentation of autonomic nervous system function [20–22]. Thus, TCPS has distinct advantages in ameliorating sleep disturbances amongst this specific demographic by bolstering both physical resilience and psychological welfare.

Regarding the clinical trial design, we attempt to enhance the validity and reliability of this trial by implementing the following key measures. First, this study will evaluate sleep quality and quality of life of college students at multiple time points including before, during, and after TCPS intervention training and follow-up through the sleep quality self-evaluation and quality of life scales, aiming to quantify the short- and long-term benefits of TCPS for insomnia. Second, we will establish three sham-controlled groups practicing fabricated TCPS regimens that separate the body and breath adjustment requirements to illustrate the advantages of synergizing the TCPS posture and abdominal breathing to modulate cerebral function and ameliorate insomnia. This will help to enhance lay comprehension of Qigong's core principle – achieving a state of harmony through the "three adjustments" of body, breath, and mind. Furthermore, we will use electrophysiological techniques to synchronously measure participants' biomechanical balance and plantar pressures, monitor their breathing and other physical parameters, and analyze their brain activity when engaging in TCPS, with the aim of evaluating consistency of participants' posture and breathing and whether they achieve the "three adjustments" of body, breath, and mind. Third, this study will reveal possible reasons why TCPS improves insomnia symptoms in college students, thereby obtaining more objective evidence to promote the application of TCPS in the management of insomnia.

Studies have shown that practicing Qigong exercises increases the alpha and theta frequency band in the frontal and the parietal cortices, suggesting that Qigong stimulates and regulates brain regions related to emotional management and sensory processing through physical movements [24, 25, 27], providing a potential neurobiological basis for the beneficial effects of Qigong in addressing psychological issues. Other than frequency, functional connectivity has been shown to match the mind adjustment of Qigong exercises [27, 42]. If TCPS has a positive effect on sleep quality, this may be reflected by an increase in functional connectivity within and between hemispheres following TCPS. Conversely, prolonged periods of stress are thought to lead to the sustained and abnormal activation of the hypothalamic–pituitary–adrenal axis, which exacerbates autonomic nervous system imbalance and ultimately culminates in chronic insomnia [45–47]. In that context, examining and evaluating respiratory function, HRV, blood pressure, and oxygen saturation could provide new information on autonomic nervous system balance and physiological reactions to help explain the physiological mechanism underlying the impact of TCPS on physical function.

However, the trial also has several potential limitations. The recruitment criteria are limited to college students aged 18–26 years with insomnia. Thus, the findings of study may not be generalizable to other age groups. Additionally, the optimal intensity and timing of TCPS remain unknown, but we believe that the TCPS scheme used in this trial will provide information for any further optimization studies. Despite these limitations, this trial represents an important milestone in the development of new therapeutic approaches for insomnia and will be easily implementable for college students with insomnia.

